
**2.2.2 Rationale for the selection of one year as the duration for Time-Limited HAART (TL-HAART)**. TL-HAART represents a compromise to maximize the potential benefit of aggressive therapeutic intervention while minimizing the potential for a negative outcome. Most of the short-term side effects of HAART are manageable either by symptomatic treatment or drug substitution. TL-HAART avoids the long-term metabolic and morphologic toxicities of HAART. TL-HAART permits more vigorous methods (such as DOT) to maximize adherence and avoid development of drug resistance since the participants will be on therapy for only one year.. The potential benefits of the intervention (enhanced host immunity and decreased establishment of viral reservoirs and quasi-species) would all be expected to take place within the first year of therapy. The rationale for the choice of one year as the duration for TL-HAART is based on studies of the immune recovery that begins when HAART is initiated. Although circulating CD4^+^ T cell levels begin to rise very soon after this time, this is mostly due to redistribution of memory cells rather than production of new (naive) cells, which requires several months to one year to occur (24). In the MACS cohort, CD4^+^ T cell counts rose for the first two years after initiation of HAART (25). Thus, one year of therapy seems a reasonable balance between the need to suppress viremia long enough to preserve HIV-specific CD4^+^ T cells without removing the antigenic stimulus for HIV-specific CD8^+^ T cells, and allowing maximal recovery of naive CD4^+^ T cells without incurring long-term toxicities of HAART.

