6.2.4 Physical Exam

Complete Physical Exam

This is required at screening, and annually thereafter. It will include height at screening, and weight at screening and then again at each subsequent time point. If at any study visit should symptoms be present which warrant a physical exam, it will be performed.

Vital Signs

Temperature, pulse, and blood pressure will be collected at all visits.

Weight

This will be recorded at each study visit.

Signs and Symptoms

Any signs or symptoms that lead to a change in treatment, regardless of grade, must be recorded on the case report forms. All signs, symptoms, and toxicities must be documented in the subject’s record, but only Grade 4 signs and symptoms must be recorded on the case report forms. All HIV related signs and symptoms, HIV-related and AIDS-defining events, deaths, and toxicities must be documented. All signs, symptoms, HIV-related and AIDS-defining events, and deaths must be recorded on the case report forms within 48 hours throughout the course of the study.

Diagnoses

All confirmed and probable diagnoses made since the last visit will be recorded in the source documentation, including current status at the time of study visit. For each diagnosis, the source document must include:

1) Date of diagnosis, date of resolution

2) Method of confirmation of diagnosis or evidence for probable diagnosis

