6.2.6 Laboratory Evaluations

Any laboratory toxicities that lead to a change in treatment, regardless of grade, must be recorded on the case report forms. At baseline, record all laboratory values. For post-baseline assessments, all laboratory values must be documented in the subject’s record but only grade 4 laboratory toxicities are to be recorded in the case report forms. Toxicities will be assessed using the Division of AIDS Table for Grading Adult Adverse Experiences,(Appendix III)

Hematology (CBC)

Hemoglobin, hematocrit, red blood cells (RBC), white blood cell count (WBC), differential WBC, absolute neutrophil count (ANC), platelets.

Chemistry Panel

Total bilirubin, AST (SGOT), ALT (SGPT), alkaline phosphatase, creatinine, indirect bilirubin, creatinine.

Lipid Panel

Total cholesterol, HDL and LDL fractionation, fasting triglycerides.

Pregnancy Test

For women with reproductive potential: Serum β-HCG or Urine test withsensitivity of 25-50 mIU/mL).

CD4 + Cell Count

Obtain absolute CD4+ cell counts and percentages at screening and at specified study visits. All laboratories performing these tests must possess a CLIA certification or equivalent. In order to perform CD4+ cell count testing that is used for patient management the laboratory also must participate in and be certified for protocol testing by the DAIDS Immunology Quality Assurance (IQA) Program, or its Canadian equivalent.

Evaluations for CD4+ cell counts should be performed at the same certified laboratory, if possible, for baseline calculation and throughout the course of the study. Because of the diurnal variation in CD4+ cell counts, determinations for individual subjects should be obtained consistently in either the morning or the afternoon throughout the study, if possible.

Note: Each time a CD4+ cell measurement is obtained, the local laboratory must perform a WBC and differential from a sample obtained at the same time.

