## 7.0 TOXICITY MANAGEMENT

##

For patients randomized to receive treatment, the HAART regimen will be selected or adjusted based on the results of the genotypic resistance test done at the time of screening. Selection and/or adjustment will be done by the study physician, who will then inform the chair or co-chair (in the case when neither the chair nor the co-chair is the treating physician) of the choice. The standard ACTG/CTN approach will be used to grade and address drug toxicity on an ongoing basis. There will be no protocol-mandated criteria for a substitution or discontinuation of HAART, such decisions being left to the standards of clinical practice, with all drug-associated toxicities being documented. Drug substitutions within the same class of drug (NRTI for NRTI, NNRTI for NNRTI or PI for PI) will be preferred, as decided by the study physician, but changes across classes will also be permitted. If the chair or co-chair of the protocol is not the treating physician, they will be informed of all decisions to change or discontinue HAART regimens on the monthly conference calls.

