### 9.5 Monitoring

The Data Safety and Monitoring Committee of the Canadian Trials Network will serve as the DSMB for this study. The study will be reviewed every six months.

HAART associated toxicity will be assessed as follows:

- Toxicity leading to treatment discontinuation
- Evaluation of Serious Adverse Events
- Evaluation of grade 3 and 4 Adverse Events

Viral load and T-cell data in the treated versus untreated groups will be compared.

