### 9.6 Analyses

Primary Endpoint

 The 24 month log plasma viral load will be compared between allocated groups on an intent-to-treat basis using linear regression to adjust for baseline plasma viral load and CD4 lymphocyte count.  All patients who have at least one post baseline visit will be included in the analysis. Patients who withdraw from follow-up prior to 24 months will have their 24 month viral load estimated using regression techniques based on group and individual trajectories.  Secondary sensitivity analyses using other analytic strategies including last observation carried forward will be used to assess the robustness of the result.

 Secondary Endpoints

Between group comparison of log plasma viral load at 36 months, and CD4 lymphocyte count at 24 and 36 months will be conducted in the same way as the analysis of 24 month viral load.

Subgroup analyses comparing treatment groups on the CD4 lymphocyte count and plasma viral load outcomes at 24 and 36 months will be carried out similarly, focusing (a) on patients treated in the acute stage and (b) patients treated early.

 A further analysis for each of the endpoints will be done using baseline CD4 lymphocyte count and plasma viral load, stage of disease, the interaction of stage and treatment, and treatment as predictors of outcome in a linear regression analysis.  This additional analysis is being done to perform formal statistical assessment of whether there are treatment by stage interactions. (The presence of an effect in one subgroup, and the lack thereof in another does not necessarily imply that the difference between the result in the two strata is statistically significant).

The toxicity of HAART will be presented using descriptive statistics as follows:

(a) percentage of patients discontinuing therapy because of toxicity

(b) percentage of patients suffering a serious adverse event (SAE)

(c) percentage of patients suffering a grade 3 or 4 adverse reaction

 All adverse events, including minor adverse events will be classified using the ACTG template.

 Confidence intervals around the percentages will be calculated.

##

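### None of the listed toxicity percentages counts a toxicity-driven change of HAART short of discontinuation, although the protocol collects the data and names tolerability as an objective

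*Protocol*

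**What the plan says.** Objective 4 in Protocol section 1.3 is the safety and tolerability of time-limited HAART. Section 9.2.2 lists toxicity in treated patients as a secondary endpoint without further definition. Section 9.6 then fixes how it will be presented, as three percentages with confidence intervals: "a) percentage of patients discontinuing therapy because of toxicity", the percentage with a serious adverse event, and "c) percentage of patients suffering a grade 3 or 4 adverse reaction". Section 9.5 gives the monitoring committee the same three topics, the first being "Toxicity leading to treatment discontinuation".

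On how toxicity will be handled, section 2.2.2 states: "Most of the short-term side effects of HAART are manageable either by symptomatic treatment or drug substitution". Section 7.0 sets no mandatory criteria either for substituting or for stopping HAART, and adds: "Drug substitutions within the same class of drug (NRTI for NRTI, NNRTI for NNRTI or PI for PI) will be preferred". Changes across classes are also allowed.

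On data capture, section 6.2.4 states: "Any signs or symptoms that lead to a change in treatment, regardless of grade, must be recorded on the case report forms". Section 6.2.6 says the same for the laboratory: "Any laboratory toxicities that lead to a change in treatment, regardless of grade, must be recorded on the case report forms". Section 6.2.3 requires interruptions, modifications and permanent discontinuation of HAART to be recorded at each visit, and sets 7 or more consecutive days as the length that makes an interruption.

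**The concern.** A drug change forced by a side effect is a direct sign of poor tolerability, even when the event is low-grade and the patient continues on another regimen. The protocol permits such changes freely and records them, but no percentage in 9.6 or item in 9.5 reports them.

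The trial sets a possible virologic benefit against the burden of a year of HAART in people who might otherwise be untreated. If part of that burden is missing from the planned toxicity summaries, readers and the monitoring committee get an incomplete account of objective 4. The data that would complete it are already required.

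**Working it through.** There is no planned figure to reproduce, because the protocol states no expected rate of toxicity, drug change or discontinuation. The check is a reading of the text, followed by an illustration under stated assumptions.

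**1. What item (a) counts.** Section 9.6 does not define discontinuing therapy. Section 7.0 names substitution and discontinuation of HAART as separate actions. Section 6.2.3 lists modifications separately from permanent discontinuation. Sections 3.0 and 5.1 use discontinuation for ending the whole treatment at 12 months. The plain reading of (a) is therefore stopping HAART.

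**2. What items (b) and (c) count.** They count serious adverse events and grade 3 or 4 reactions, whatever was done with the drug.

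**3. Typical records scored on that reading.**

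| Patient record | (a) | (b) | (c) |
|---|---|---|---|
| Grade 2, non-serious; one NRTI replaced by another; stays on HAART | no | no | no |
| Grade 2, non-serious; NNRTI replaced by a PI; stays on HAART | no | no | no |
| Grade 3, non-serious; one drug replaced; stays on HAART | no | no | yes |
| Serious adverse event of grade 3 or 4; one drug replaced; stays on HAART | no | yes | yes |
| Grade 2, non-serious; all HAART stopped for good | yes | no | no |

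The first two rows are the gap. A toxicity-driven interruption with later resumption is not settled by the text. Section 8.0, which gives the criteria for treatment discontinuation, covers temporary as well as permanent stopping for a medical condition.

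**4. Are the data collected?** Yes. Under 6.2.4 and 6.2.6, any toxicity that changes treatment is entered whatever its grade. For post-baseline laboratory toxicities below grade 4, a treatment change is the only trigger for entry in 6.2.6. The protocol thus singles these events out for capture.

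**5. How large could the gap be?** Take the patients with treatment-changing toxicity. Let *s* be the share whose treatment is changed short of discontinuation, and *g* the share of those whose event is grade 1-2 and non-serious. The share in none of (a)-(c) is *s* × *g*. The protocol gives neither value, so both are assumptions.

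| | g = 0.25 | g = 0.50 | g = 0.75 |
|---|---|---|---|
| s = 0.5 | 12.5% | 25% | 37.5% |
| s = 0.7 | 17.5% | 35% | 52.5% |
| s = 0.9 | 22.5% | 45% | 67.5% |

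Section 9.4 plans 90 patients per group. Assume that 20% of the treated arm, 18 patients, have treatment-changing toxicity. The number uncounted then runs from 18 × 0.125 = 2.25 to 18 × 0.675 = 12.15, or about 2 to 12.

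On the same assumption, item (a) would show 18 × (1 − 0.5) = 9 of 90 at s = 0.5, which is 10% (exact 95% interval 4.7% to 18.1%). At s = 0.9 it would show 18 × (1 − 0.9) = 1.8, about 2 of 90, which is 2.2% (0.3% to 7.8%). The share with any toxicity-driven change would be 18/90 = 20% in both cases.

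**6. When would more than half be uncounted?** This needs *g* > 0.5/*s*: above 0.71 at s = 0.7, above 0.625 at s = 0.8, and above 0.56 at s = 0.9. It cannot happen at s of 0.5 or less.

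**The case against.** Several objections have force.

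- **Other toxicity reporting is planned.** Section 9.0 promises descriptive statistics for drug toxicity and for treatment discontinuation. Section 9.6 says that all adverse events, minor ones included, will be classified by the ACTG template. This is true, but neither sentence names a summary that links an event to a drug change. Section 9.6 lists its percentages explicitly, so an analysis plan that follows it would carry the gap forward.
- **Item (a) is undefined.** If it means stopping any single drug, substitutions are counted and the gap largely closes. That reading is possible, though the usage in 6.2.3 and 7.0 points the other way. The two readings give different percentages, so a definition is needed in either case.
- **Nothing is decided on this endpoint.** Toxicity is a descriptive secondary endpoint with no test or threshold. This stands, and it limits the weight of the point.
- **Switching is partly discretionary.** In an open-label trial with no mandatory criteria, some swaps will reflect preference. This also stands. It is a reason not to let a composite displace complete stopping as a reported figure.

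A reader might go further and infer that toxicity will be handled mainly by substitution, so that most treatment-limiting toxicity escapes all three percentages. The documents do not support this. Section 2.2.2 offers symptomatic treatment or substitution without ranking them. The preference in 7.0 sets within-class against cross-class changes, not substitution against stopping. Items (b) and (c) count severe and serious events whether or not the drug was changed.

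**Conclusion.** The point holds in limited form. On the plain reading of discontinuation, a toxicity-driven change of HAART for a grade 1-2, non-serious event is in none of the percentages in 9.6 or the items in 9.5, although it must be recorded and bears directly on objective 4.

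The size is unknown. The range of 12.5% to 67.5% uncounted, or about 2 to 12 of an assumed 18 affected patients among 90, rests wholly on assumed values of *s* and *g* and an assumed 20% rate. Seven of the nine combinations lie below one half.

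It would also be wrong to say that item (a) understates toxicity by a given factor. If one assumes that 1 in 5 toxicity-driven changes ends in stopping, a fivefold difference follows, but it only restates the assumption. It also leaves out patients already counted in (b) or (c).

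This is a low-cost improvement in reporting. It does not affect the primary analysis or the sample size.

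**What to change.** 1. In 9.6, keep item (a) and state that it means discontinuation of all HAART because of toxicity.
2. Add a further item to 9.6: *percentage of patients with any toxicity-driven change of HAART (substitution, dose change, interruption of 7 or more consecutive days, or discontinuation)*. Show each component separately, with confidence intervals.
3. Add the same item to the toxicity list in 9.5.

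Report the new item beside (a)-(c), not in place of (a), so that complete stopping stays visible and discretionary switching does not blur it.

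The cost is about one added line in each section and the definition of (a). The toxicities and modifications are already required on the case report forms. The forms are not shown, so the sponsor should confirm that each recorded change can be linked to the toxicity behind it. No sample size changes, and no change to how toxicity is managed is proposed.

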## 10.0 PHARMACOLOGY PLAN

*NOT APPLICABLE*

###

### 10.1 Pharmacology Objectives

###

### 10.2 Pharmacology Study Design

###

### 10.3 Primary and Secondary Data, Modeling, and Data Analysis

###

### 10.4 Anticipated Outcomes

## 11.0 DATA COLLECTION AND MONITORING AND ADVERSE EXPERIENCE REPORTING

### 11.1 Records to Be Kept

Case report forms will be provided for each subject. Subjects must not be identified by name on any case report forms. Subjects will be identified by the patient identification number (PID) and study identification number (SID) provided by the Canadian HIV Trials Network Data Management Center upon randomization.

### 11.2 Role of Data Management

11.2.1 Instructions concerning the recording of study data on case report forms will be provided by the Canadian HIV Trials Network Data Management Center. Each study site is responsible for keying the data in a timely fashion.

11.2.2 It is the responsibility of the Canadian HIV Trials Network Data Management Center to assure the quality of computerized data for this study. This role extends from protocol development to generation of the final study databases.

###

### 11.3 Clinical Site Monitoring and Record Availability

11.3.1 Site monitors under contract to the National Institute of Allergy and Infectious Diseases (NIAID) will visit participating clinical research sites to review the individual subject records, including consent forms, case report forms, supporting data, laboratory specimen records, and medical records (physicians’ progress notes, nurses’ notes, individuals’ hospital charts), to ensure protection of study subjects, compliance with the protocol, and accuracy and completeness of records. The monitors also will inspect sites’ regulatory files to ensure that regulatory requirements are being followed.

11.3.2 The investigator will make study documents (e.g., consent forms, drug distribution forms, case report forms) and pertinent hospital or clinic records readily available for inspection by the local IRB, the site monitors, the NIAID, the Office for Human Research Protections (OHRP), or other regulatory authorities for confirmation of the study data.

### 11.4 Serious Adverse Experience (SAE) Reporting

11.41 Serious adverse experiences must be documented on the Division of AIDS Serious Adverse Experience (SAE) Reporting Form and submitted to DAIDS through the Regulatory Compliance Center (RCC) and are defined in the current DAIDS *Serious Adverse Experience (SAE) Reporting Manual.* For SAE reporting of laboratories or medical conditions not found on the DAIDS table for Grading Adult Adverse Experiences (Appendix III), refer to “estimating severity grades scale” found in the SAE section of the DAIDS Serious Adverse Experience (SAE) Reporting Manual.

11.42 Participating sites will be provided with the following materials:

- DAIDS Policy for SAE Reporting on Non-IND Studies
- DAIDS SAE Reporting Manual
- DAIDS Table for Grading Severity of Adult Adverse Experiences
- DAIDS Serious Adverse Events (SAE) Form

11.43 Sites must also adhere to local regulatory agency (IRB) requirements for serious adverse event  reporting. Specifically, for Baltimore, all SAEs will be reported to the Johns Hopkins Bloomberg School of Public Health Committee on Human Research, and Canadian sites will notify their local IRBs. Any safety reports submitted by sites to the local regulatory authority must be kept in the essential documents file. These reports must be submitted to the DAIDS Clinical Representative.

11.44 All SAEs will be reported to the medical monitor for this study within 3 working days of notification of the event. The medical monitor for this study is:

[name] [name]

[contact]

[contact]

## 12.0 HUMAN SUBJECTS

###

### 12.1 Institutional Review Board (IRB) Review and Informed Consent

This protocol and the informed consent document (Appendix I) and any subsequent modifications will be reviewed and approved by the IRB or ethics committee responsible for oversight of the study. A signed consent form will be obtained from the subject. The consent form will describe the purpose of the study, the procedures to be followed, and the risks and benefits of participation. A copy of the consent form will be given to the subject, and this fact will be documented in the subject’s record.

### 12.2 Subject Confidentiality

All laboratory specimens, evaluation forms, reports, and other records that leave the site will be identified by coded number only to maintain subject confidentiality. **All records will be kept locked.** All computer entry and networking programs will be done with coded numbers only. Clinical information will not be released without written permission of the subject, except as necessary for monitoring by IRB, the NIAID, the OHRP, or other regulatory authority.

### 12.3 Study Discontinuation

The study may be discontinued at any time by the IRB, the NIAID, or other government agencies as part of their duties to ensure that research subjects are protected.

#

## 13.0 PUBLICATION OF RESEARCH FINDINGS

Publication of the results of this trial will be governed by the policies of the Acute Infection Early Disease Research Program (AIEDRP), of which both [name] and [name] (chair and co-chair of this protocol) are members of the executive committee.

## 14.0 BIOHAZARD CONTAINMENT

As the transmission of HIV and other blood-borne pathogens can occur through contact with contaminated needles, blood, and blood products, appropriate blood and secretion precautions will be employed by all personnel in the drawing of blood and shipping and handling of all specimens for this study, as currently recommended by the Centers for Disease Control and Prevention and the National Institutes of Health.

All infectious specimens will be transported using packaging mandated in the Code of Federal Regulations, 42 CFR Part 72. Please also refer to individual carrier guidelines, e.g., Federal Express, Airborne Express, for specific instructions.

